## Method

### Study design and randomisation

This study is a randomised controlled trial (RCT) with a one-year prospective follow-up. Simultaneously, an economic evaluation will be conducted. The Medical Ethics Committee of the VU University Medical Center has approved the study design, protocols and informed consent procedures. Figure 1 shows the design of the study. Potential participants are contacted and after signing informed consent a validated fall risk profile [16] is used to select participants with a high risk of recurrent falling (score of 8 and higher). Participants with a low-risk of recurrent falling are excluded from the RCT. Participants living in a residential home are right away assigned to the high-risk group, which is in accordance with the recommendations of the Dutch Institute for Healthcare Improvement (CBO) guideline [25]. Participants in the high-risk group are blindly randomised into two groups: the intervention group and the usual care group. Prior to the onset of the trial a randomisation schedule is made by a statistician. A block randomisation of 4 per block is used. Using the sequence of this schedule, opaque envelopes are numbered and filled with group names. When a participant is designated to the high-risk group, the interviewer, who is unaware of the content, opens the envelope with the lowest number.

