### Procedure

All persons who consult the emergency department or primary care physician after a fall receive usual care. Within two weeks after the initial presentation, written information is sent and several days thereafter, the potential participants are contacted by telephone. All actual participants (who sign informed consent) are visited at their homes by a trained interviewer within 3 months after the fall incident. During the first home visit, the fall risk profile [16], fall history, independence in activities of daily living, quality of life and physical performance are measured. All high-risk participants will report falls during at least one year using a fall calendar and receive a cost-evaluation questionnaire at 3, 6 and 12 months after the first home visit. The times to first and second fall are the primary outcome measures. One year after the first home visit, they are visited a second time to reassess the activities of daily living, quality of life and physical performance. Scores on these questionnaires and tests are used as secondary outcome measures. Furthermore, the treatment adherence and medication use are evaluated. Table 1 presents an overview of the procedure and measurements. The measurements used are described later on in this article.

**Table 1 T1:** Overview of procedure and measurements

	Months	Measurements	Purpose
1st home visit	0	fall risk profile	selection high risk participants
		fall history	assessment of fall risk factors, confounders
		activities of daily living	secondary outcome measure
		quality of life	secondary outcome measure
		medication use	assessment of fall risk factors
		medical history	assessment of fall risk factors, confounders
		physical performance	secondary outcome measure
1st follow-up	3	1st calendar sheet	primary outcome measure
		3 months cost-evaluation	primary outcome measure
2nd follow-up	6	2nd calendar sheet	primary outcome measure
		6 months cost-evaluation	primary outcome measure
3rd follow-up	9	3rd calendar sheet	primary outcome measure
2nd home visit	12	activities of daily living	secondary outcome measure
		quality of life	secondary outcome measure
		medication use	treatment adherence
		medical history	secondary outcome measure, confounders
		physical performance	secondary outcome measure
		treatment adherence	confounder, to enhance the interpretation of the results
4th follow-up	12	4th calendar sheet	primary outcome measure
		12 months cost-evaluation	primary outcome measure

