#### Follow-up

At the first home visit the participants receive a fall calendar [16]. For the period of one year, the participants tick per week whether they did or did not fall during that week. A fall is defined as an unintentional change in position resulting in coming to rest at a lower level or on the ground [41]. Once per 3 months the participants return a calendar sheet by mail. When no sheet is received, or when the sheet is completed incorrectly, we inquire by telephone whether, and if yes, when the participant has fallen in the past 3 months.

The cost-evaluation questionnaire registers the costs made to prevent a new fall or the consequences of a new fall. The questionnaire assesses: the number of visits to physicians, therapists or day care centres; amount and aim of surgical procedures; number of days of admission to a hospital, home or nursing home; purchase of aids and adaptations in the home environment. The questionnaires are conducted 3, 6 and 12 months after the first home visit. The 3 and 6 months questionnaires are sent by mail and apply to the preceding 3 months. The 12 months questionnaire is assessed during the interview of the second home visit. This questionnaire applies to the preceding 6 months. When no questionnaire is received, or when it is completed incorrectly, the questionnaire will be completed by telephone.

During the second home visit, one year after the first visit, the same physical performance tests are conducted along with a reassessment of fall related healthcare costs, medical history, medication use, quality of life and activities of daily living. In addition, in the intervention group, adherence to the treatment regimen is evaluated. Treatment adherence in the intervention group is evaluated per recommendation given. Recommendations regarding changes in medication are evaluated by reassessing the medication use as described above. Adherence to all other recommendations (such as referrals to physical therapy or cardiologist) is assessed by asking whether, to what extent, and how the recommendations of the intervention were effected. The information from the participant is completed with information from the rapports of the involved specialists.

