### Statistics

Data will be primarily analysed according to the intention-to-treat principle, i.e., including all randomized participants, regardless of whether they received or did not receive the intervention. Subsequently, the results of the intention-to-treat analysis will be compared with the results of an on-treatment analysis.

At baseline, differences in baseline characteristics will be compared between the intervention and control group to examine comparability between the two groups.

To examine the effectiveness of the multidisciplinary transmural care, Cox proportional hazards regression will be conducted, with time to first fall and time to second fall within one year of follow-up as outcome measures, and with age, gender and living situation as covariables. Subsequently, multiple linear regression analyses will be used to compare differences in secondary outcome measures (ADL-score, QoL, physical performance and morbidity data) at 12 months follow-up between intervention and control group.

The economic evaluation will be conducted from a societal perspective, which implies that all costs and outcomes are taken into account. The economic evaluation will involve calculating cost-effectiveness and cost-utility ratios. The incremental costs and effects of the intervention will be compared with usual care. The difference in costs of the intervention group and usual care group will be computed using bootstrapping techniques. Uncertainty ratios will be presented on cost effectiveness and cost utility planes. Acceptability curves will also be estimated. These present the probability that the intervention is cost-effective given a ceiling ratio that policy makers are willing to invest.

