## Discussion

The strengths of this study, are the screening of participants at high risk of falling, its transmural design and evaluation of treatment adherence. In previous studies [13,42], as in our study, participants were selected at accident and emergency departments or primary care centres. These participants are a mix of once-fallers and recurrent fallers. In previous studies, the participants assigned to the intervention group were not selected for risk of falling. We expect that participants at high risk of recurrent falling will benefit most from the intervention and, therefore, we expect to find an enhanced (cost-) effectiveness of the preventive measures.

Furthermore, in previous studies, the recommendations of the intervention were drawn up by the geriatrician and executed by the primary care physician [13,42], whereas in this study, the primary care physician is actively involved in the process of drawing up the recommendations, and the intervention is initiated by the geriatrician and followed up by both the geriatrician and primary care physician. We therefore expect to have a better coordination of the transmural care.

In several fall prevention studies, active participation has been associated with better outcomes [43,44] and poor treatment adherence has been reported as a possible explanation for lack of effect of the intervention [45]. In contrast to previous studies [13,42,43], we not only score the number of recommendations that are effected, but also add an evaluation of how the treatment recommendations are effected. This information will add to the interpretation of the results [44].

The results of this trial will provide clinicians in the field of aging with more knowledge on treatment of older persons at high-risk of recurrent falling. If proven cost-effective, a multidisciplinary assessment and treatment of fall risk factors in persons with a high risk of recurrent falling will lower the risk of falling and consequently lead to reduced incidence and costs of falls.

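### The planned cost comparison is valid for persons already identified as high risk, but it omits the cost of finding them and so understates the cost of a screen-then-treat strategy starting from all fallers

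*Protocol article*

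**What the plan says.** **Screening comes before randomisation.** The Procedure section opens its list of baseline measurements with "During the first home visit, the fall risk profile [16], fall history, independence in activities of daily living". The visit is made at home by a trained interviewer. Under Study design and randomisation, a score of 8 or more defines high risk, and "Participants with a low-risk of recurrent falling are excluded from the RCT". Then: "Participants in the high-risk group are blindly randomised into two groups: the intervention group and the usual care group". There is one route that needs no score: "Participants living in a residential home are right away assigned to the high-risk group".

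**The intervention is defined as starting later.** The Intervention section begins it at the geriatric outpatient clinic. The Usual care section describes the comparator as mainly treating what the fall has caused, with systematic risk assessment only incidental.

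**Costs are collected from the home visit onward.** Follow-up states: "The questionnaires are conducted 3, 6 and 12 months after the first home visit". The listed items are care contacts, surgery, admissions, aids and home adaptations. The screening visit is not among them.

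**The economic result is a difference between the arms.** In Statistics, "The incremental costs and effects of the intervention will be compared with usual care", with the cost difference bootstrapped and acceptability curves drawn for policy makers. The perspective is societal, which the section explains as counting every cost and outcome.

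**The Discussion credits selection.** It names screening for high risk among the trial's strengths, notes that earlier trials did not select on risk, and for that reason expects better cost-effectiveness. Its last sentence opens "If proven cost-effective, a multidisciplinary assessment and treatment of fall risk factors in persons with a high risk of recurrent falling" and goes on to predict fewer falls and lower costs of falls.

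**The concern.** A payer who wants to act on this trial starts from older people who present to an emergency department or primary care physician after a fall. The high-risk group must first be found among them, and by the article's own account usual care does not do this routinely. Case-finding is therefore an added cost of the strategy when it is applied to all fallers.

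The trial design removes that cost from the comparison. A longer list of unit costs would not restore it: if the visit were costed for every randomised participant, it would add the same amount to both arms and cancel, and the visits to people screened out would still be missing.

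At stake is what the ratios and acceptability curves can support. The Discussion expects an economic gain from targeting high-risk persons, while the planned difference leaves out what the targeting costs.

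**Working it through.** **No economic figure to reproduce.** The article gives no unit cost, incremental cost or ratio. The nearest figure is the share scoring 8 or more in Table 2, so that is checked first.

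**Inputs from Table 2, cut-off 8:** share at high risk 32.6%, sensitivity 52.1%, specificity 71.2%, positive predictive value 54.0%, negative predictive value 69.6%. The stated base is 426 fallers.

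**Reproducing the 32.6%.** The printed sensitivities and specificities fit 144 recurrent and 222 non-recurrent fallers, 366 in all:
- true positives: 75 (75/144 = 52.1%)
- true negatives: 158 (158/222 = 71.2%), so false positives are 222 − 158 = 64
- all positives: 75 + 64 = 139
- positive predictive value: 75/139 = 54.0%, as printed
- negative predictive value: 158/(158 + 69) = 158/227 = 69.6%, as printed
- share flagged on 426: 139/426 = 32.6%, as printed
- share flagged on 366: 139/366 = 38.0%

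The printed share thus uses 426 as its base, while the other columns fit 366. The article does not explain the difference of 60, so both shares are carried forward.

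**Screenings per high-risk person.** With q the share flagged, finding one high-risk person takes 1/q screenings, and finding 200 through the score takes 200/q (rounded up). The notes to Table 2 expect higher scores in this trial than in the reference cohort but give no figure. The 50% and 70% rows are assumptions.

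| q | Source | Screenings per high-risk person (1/q) | Screenings for 200 |
|---|---|---|---|
| 32.6% | Table 2, base 426 | 3.07 | 614 |
| 38.0% | Table 2, base 366 | 2.63 | 527 |
| 50% | assumed | 2.00 | 400 |
| 70% | assumed | 1.43 | 286 |

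**Where the cost goes.** Let S be the cost of applying the risk profile once, ΔC the planned cost difference per participant and ΔE the effect difference.
- Within the trial, each randomised participant in either arm has been screened once: S − S = 0. Persons screened out contribute to neither arm.
- Compared with no screening, screen-then-treat costs ΔC + S/q per person treated.
- If screening by itself changes neither falls nor other costs, the effect per person treated stays ΔE. The ratio then moves from ΔC/ΔE to (ΔC + S/q)/ΔE.

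The amount left out is S/q per treated person. S is not given. Purely to show scale, an assumed S of 100 units leaves out about 307, 263, 200 or 143 units for the four rows. Neither ΔC nor ΔE is given, so the relative change in the ratio cannot be worked out.

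**Residential-home participants.** They are high risk without needing a score, so S/q does not apply to them. If they make up a fraction r of those treated, the average amount left out is (1 − r) × S/q, with q taken among persons who do need the score. The article does not give r.

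**The case against.** The strongest reply is that the trial asks a narrower question. The Abstract and the stated objective concern older persons with a high risk of falling, and the intervention starts at the clinic. For that question a cost common to both arms should cancel. **This stands.** A reader might infer that the planned ratios are simply biased in favour of the intervention, or that the article presents them as the cost-effectiveness of a programme for all fallers. The documents do not support either reading. The within-trial contrast is unbiased for identified high-risk persons, and the Discussion's closing sentence is conditional and names that group.

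A second reply is that an article leaves its costing list to a fuller plan and that the patient questionnaire need not be the only cost source. **This stands in part.** The article nowhere says that screening will go uncosted. But costing it in both arms would still give a difference of zero. Only a deliberate charge to the intervention side changes the result, and the stated comparison contains none.

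A third reply concerns size. The home visit also collects fall history, daily functioning, quality of life, medication and physical performance, so most of it is research measurement. The profile itself is five questions, two measurements and two interaction items. Residential-home participants need no score, the base of Table 2 is uncertain, and practice might find cases without a home visit. **All of this stands.** It makes the omitted amount smaller and less certain, and it rules out using the cost of the whole visit. It does not bring the amount to zero.

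**Conclusion.** The point holds within limits. The planned cost difference answers the question for persons already identified as high risk. It contains no case-finding cost, so it understates the incremental cost of screening all fallers and treating those flagged. The direction is certain for that wider strategy as long as applying the profile costs something and usual care does not routinely do it.

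The size in screenings is about 2.6 to 3.1 per person scoring 8 or higher if Table 2 carries over, and about 1.4 to 2.0 if 50% to 70% score that high. The monetary size and the effect on the ratio and acceptability curves remain unknown.

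It merits a change because the Statistics section says that all costs are counted, the curves are meant for policy makers, and the Discussion attributes enhanced cost-effectiveness to selection without setting the cost of selection against it.

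**What to change.** 1. Keep the planned cost-effectiveness and cost-utility ratios, and label them as applying to persons already identified as high risk.
2. Add a second cost-effectiveness, cost-utility and acceptability analysis, labelled as the screen-then-treat strategy. To each intervention participant who entered through the score, add the unit cost of applying the risk profile (not of the whole research visit) times number screened / number flagged, from the trial's screening log. Leave residential-home participants out of that fraction and out of the charge. Add nothing to usual care.
3. State the unit cost and its source, and vary it over a range.
4. If the second analysis is not done, limit the economic conclusion explicitly to persons already identified as high risk.

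The cost is one extra unit cost and a repeat of the bootstrap. No new participant data are needed beyond the screening log. The downside is a less favourable ratio for the wider strategy.

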### Study population

The study population consists of persons of 65 years and over, who consult the Accidents and Emergency Department of the VU University Medical Center (Amsterdam, The Netherlands) or their primary care physician between April 2005 and April 2007 after a fall incident. Inclusion criteria are living independently or in a residential home, living in the vicinity of the VU University Medical Center and having experienced a fall. Exclusion criteria are inability to sign informed consent, inability to provide a fall history, fall due to a traffic or occupational accident, living in a nursing home and acute pathology requiring long-term rehabilitation, such as a stroke.

200 high-risk participants will be included in the intervention study, of which we will enrol 100 participants in the intervention group and 100 in the control group. With a significance level of 0.05, a power of 80% and an expected difference in fall incidence of 50% [13] between the intervention and control group, 57 participants are needed both in the intervention and in the control group. Taking into account a drop-out rate of 30% a minimum of 82 participants are needed in each group. With 100 persons in both the intervention and control group, the numbers are certainly high enough to detect statistical significant differences.

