Fall history is assessed with the fall history instrument (Carefall Triage Instrument, version 007), which is a questionnaire developed by the Academic Medical Center, the VU University Medical Center and the Erasmus Medical Center, The Netherlands. The fall history collects data on the circumstances of the last and previous falls, mobility and risk factors of bone loss and osteoporosis, social status and general health. Medical history is assessed using a questionnaire on self-reported (chronic) diseases both in the past and present. The questionnaire includes 7 major chronic diseases, i.e. chronic lung diseases, cardiac diseases, vascular diseases, stroke, diabetes mellitus, malignant neoplasms and joint disorders (i.e. osteoarthritis and rheumatoid arthritis). In addition, participants are asked to indicate any other chronic disease, including psychological diseases, which they have or have had. Medication use is assessed by directly copying the names of drugs used in the previous two weeks from the containers. The name, doses per unit, number of times taken per day, time of administration, doses per intake, purpose, prescription or over the counter (OTC) and whether the drug has been prescribed after the fall are assessed for each drug. This information is compared to medication records of the public pharmacy. Level of independence in activities of daily living (ADL) will be examined using the Barthel Index (range 0, fully dependent, to 20, fully independent) [33]. The level of functioning on more complex daily activities will be examined using a scale of instrumental ADL introduced by Lawton and Brody (range 0, fully dependent, to 8, fully independent) [34]. Quality of Life (QoL) is examined using the Dutch translations of the SF-12 and the EQ-5D. The SF-12 consists of 12 items and is a abbreviated version of the SF-36 [35]. The SF-12 has been designed and validated to measure health related QoL in large population studies [35,36]. The EQ-5D (EuroQol) has been developed to generate a general index of experienced health and for the assessment of Quality Adjusted Life Years (QALY). It is therefore suitable for economic evaluations [37]. The assessment consists of 5 items (mobility, self-care, usual activities, pain/discomfort and anxiety/depression) and a visual analogue scale (0, worst, to 100, best imaginable health state) [37]. The fall history, ADL and QoL questionnaires are sent to the participants prior to the first home visit. Participants are asked to complete these questionnaires before the home visit. The visiting researcher assists participants who are unable to complete these questionnaires independently.

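### The cost-utility comparison names no adjustment for baseline EQ-5D utility; with utility measured only at months 0 and 12, adjusting would make the incremental QALY clearly more precise at almost no cost

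*Protocol article*

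**What the plan says.** On the economic evaluation, the Statistics section of the protocol article states: "The economic evaluation will involve calculating cost-effectiveness and cost-utility ratios". On the effect side it adds only: "The incremental costs and effects of the intervention will be compared with usual care". Bootstrapping is mentioned for the difference in costs. Cost-effectiveness and cost-utility planes and acceptability curves are also planned. No covariates are named in this paragraph. In the same section, age, gender and living situation are named as covariates for the Cox models of time to first and second fall.

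The Baseline assessment section introduces the EQ-5D as the instrument from which QALYs can be obtained. Table 1 lists quality of life at the first home visit (month 0) and the second home visit (month 12). The Follow-up section itemises the content of the cost questionnaire used at 3 and 6 months, and the EQ-5D is not in that list.

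On allocation, the Study design and randomisation section says "A block randomisation of 4 per block is used". It mentions no stratification.

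**The concern.** When utility is measured twice, at the start and end of one year, the usual area-under-the-curve QALY gives each measurement half the weight. The first half is recorded around the first home visit, before the intervention begins at the geriatric outpatient clinic, so the intervention cannot change it. Nothing described in the randomisation balances baseline utility. If the arms happen to differ at month 0, that difference goes straight into the incremental QALY.

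This goes beyond leaving a useful covariate out of a model for a 12-month score. There the gain from adjustment vanishes when baseline and follow-up are uncorrelated. Here the baseline is a component of the outcome, so precision is lost even at zero correlation.

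The incremental QALY is the denominator of the cost-utility ratio and one axis of the cost-utility plane, and the cost-utility acceptability curve depends on it. Cost-effectiveness is part of the stated aim of the trial.

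**Working it through.** **The article's own figures.** It gives none for the QALY comparison. Its only sample-size figures concern falls: "57 participants are needed both in the intervention and in the control group", rising to 82 with 30% drop-out. Taking a control risk of 0.50 (not stated) halved to 0.25, two-sided 0.05 and 80% power, I get 58 per arm; a control risk of 0.505 gives exactly 57. Then 57/0.70 = 81.4, rounded up to 82. These figures are consistent with each other, and all that is needed from this section is the arm size: "we will enrol 100 participants in the intervention group and 100 in the control group". With 30% drop-out, 100 x 0.70 = 70 per arm remain.

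**Assumptions not in the article.** The QALY is Q = (u0 + u12)/2. Utility has the same standard deviation s at both times, with s = 0.25 (range 0.20 to 0.30). The correlation rho between u0 and u12 runs from 0 to 0.7.

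**Formulas.**
- Unadjusted variance per person: Var(Q) = s²(1+rho)/2.
- The slope of Q on u0 is (1+rho)/2, so the variance after adjustment is s²(1+rho)/2 - s²(1+rho)²/4 = s²(1-rho²)/4.
- Standard error of the arm difference: sqrt(2 x variance / n per arm).
- Ratio of standard errors, unadjusted to adjusted: sqrt(2/(1-rho)). It does not depend on s or n.

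**Results with s = 0.25.**

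| rho | ratio | SE at 100 per arm, unadjusted / adjusted | SE at 70 per arm, unadjusted / adjusted |
|---|---|---|---|
| 0 | 1.41 | 0.0250 / 0.0177 | 0.0299 / 0.0211 |
| 0.3 | 1.69 | 0.0285 / 0.0169 | 0.0341 / 0.0202 |
| 0.5 | 2.00 | 0.0306 / 0.0153 | 0.0366 / 0.0183 |
| 0.7 | 2.58 | 0.0326 / 0.0126 | 0.0390 / 0.0151 |

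At rho 0.5 and 100 per arm, s = 0.20 gives 0.024 / 0.012 and s = 0.30 gives 0.037 / 0.018. A simulation of 4,000 trials with s = 0.25, rho 0.5 and 100 per arm gave standard errors of 0.0310 and 0.0153, a ratio of 2.02. Both mean differences were essentially zero, so neither estimator is biased.

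**Effect of a chance imbalance.** The standard error of the baseline difference is 0.25 x sqrt(2/100) = 0.035. An imbalance of that size moves the expected unadjusted QALY difference by 0.035 x (1+rho)/2, which is about 0.027 at rho 0.5. Of this, 0.018 enters directly through u0 and the rest through the correlation with u12.

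**Other ways of building the effect, at rho 0.5.**
- EQ-5D also taken at 3 and 6 months: ratio 1.41 with equal correlations, 1.72 with correlation decaying over time.
- Month-12 utility alone: adjustment removes rho² = 25% of the variance.
- Change from baseline: adjustment removes (1-rho)/2 = 25% of the variance.

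The size of the gain depends on the construction; at this correlation its direction does not.

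**The case against.** The strongest reply is that the article is silent, and silence is not a decision. A reader might infer that the plan fixes an unadjusted comparison, but the text does not say so: a regression of QALYs on arm and baseline utility would fit the quoted sentence unchanged. A design article gives the economic evaluation one paragraph, and model covariates are often left to the full protocol or analysis plan. This stands, and it is why the point is an improvement and not an error or a contradiction.

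Four further points also stand:

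- The QALY formula is inferred from the measurement schedule. Bootstrapping of QALYs is likewise inferred, from the planned planes; the article assigns bootstrapping only to costs.
- Doubling of the standard error is the value at rho 0.5, not a ceiling.
- No significance test on QALYs is planned, so power is only illustrative. For a month-12 gain of 0.4 s, with rho 0.5 and 100 per arm, a two-sided 0.05 test would have 37% power unadjusted and 90% adjusted.
- The time-to-fall outcomes are untouched, and Table 1 labels quality of life a secondary outcome.

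The planned check of baseline comparability is a weaker defence. It may reveal an imbalance but does not remove it from the QALY difference, and a decision to adjust taken after seeing it would no longer be prespecified. Nor does the linear regression planned for 12-month quality of life cover the QALY comparison.

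**Conclusion.** The point holds as a nearly free gain in precision that the described analysis does not secure. As written, the incremental effect is a comparison with usual care without named covariates, while the one covariate that would form half of the natural QALY is already collected.

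If the comparison is run unadjusted, its standard error is between 1.4 times (rho 0) and 2.6 times (rho 0.7) the adjusted one. This rests on the two-point QALY, equal variances and an assumed correlation. The ratio is smaller, but still above 1 at rho 0.5, under the other constructions examined.

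A reader might go further and conclude that the cost-utility result would be biased or its uncertainty misstated. The document does not support that. Under randomisation the unadjusted difference is unbiased on average and its wider standard error is valid. The cost is lost precision, and sensitivity of this one trial's ratio, plane and curve to a chance imbalance. The effect on the acceptability curve itself was not computed; it also depends on cost variation and the ceiling ratio.

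**What to change.** In the economic paragraph of the Statistics section, or in the analysis plan it relies on, state how QALYs are computed from the EQ-5D and add the following:

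- The incremental QALY is the arm coefficient from a linear regression of QALYs on arm and baseline EQ-5D utility, together with age, gender and living situation as in the Cox models.
- The regression is refitted in each bootstrap resample, with each participant's costs and QALYs resampled together.
- The adjusted estimate feeds the cost-utility ratio, plane and acceptability curve.
- The unadjusted difference is reported as a sensitivity analysis.

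The change costs a few sentences and one regression per resample, with no new data and no extra participants. The small downside is that participants with a missing baseline EQ-5D need baseline imputation. They should be few, because the questionnaire is sent before the first home visit and the visiting researcher helps those who cannot complete it alone. The article places the start of data analysis after follow-up ends in July 2008, so the wording can be settled before then.
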